### Frequency and plans for auditing trial conduct {23}

Study monitoring will be provided by the responsible monitor(s) at the Menzies School of Health Research (or designee) in accordance with the Monitoring Plan and “International Conference on Harmonisation of Technical Requirements for Registration of Pharmaceuticals for Human Use” Good Clinical Practice.

The responsible monitor will visit each study site at least once per year and will be allowed, on request, to inspect the various records (source documents, paper CRFs, eCRFs and other pertinent data) provided that participant confidentiality is maintained in accord with local requirements.

It will be the monitor’s responsibility to inspect the eCRFs throughout the study, to verify the adherence to the protocol and the completeness, consistency and accuracy of the data being entered on them. The monitor must verify that the participant received the study drug as randomised. The monitor should have access to laboratory test reports and other participant records needed to verify the entries on the eCRF. The investigators and site staff and teams agree to cooperate with the monitor to ensure that any problems detected in the course of these monitoring visits are resolved in a timely manner.

#### Safety

All the trial medications are licenced for use in Australia with established safety profiles and routinely used in clinical practice. A safety measure was written into the protocol to avoid putting participants at risk of either excessive or insufficient IV iron administration according to the current standards for haemodialysis patients. Prior to receiving any study treatment, participants’ blood results are reviewed for ferritin and TSAT levels; participants’ treatment varies based on the results of these blood levels:
Assigned study drug will be administered for ferritin levels between ≥ 700 μg/L and ≤ 2000 μg/L and TSAT < 40% and ferritin < 700 μg/L and TSAT < 40% (Arm A) and no treatment for ferritin levels between ≥ 700 μg/L and ≤ 2000 μg/L and TSAT < 40% (Arm B) and rescue therapy for ferritin levels < 700 μg/L and TSAT< 40% (both arms)For both Arms A and B, if ferritin levels are < 700 μg/L *and* TSAT < 40%, “rescue treatment” will be administered for that month.If ferritin > 2000 μg/L and/or TSAT ≥ 40% for both Arms A and B, study treatment will be withheld and receive no treatment for that month.

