### Intervention description {11a}

#### Treatment of study participants

Participants are randomised to either Arm A: Intervention IV Iron treatment group (Figs. 1 and 2), or Arm B: Control group receiving no intravenous iron treatment (Figs. 1 and 2). After the randomisation, participants receive monthly treatment as per their randomisation of either monthly intravenous iron if serum ferritin ≥ 700 μg/L and ≤ 2000 μg/L and TSAT < 40% (Arm A) or no IV iron treatment (Arm B) for up to 36 months. Study treatment is withheld if monthly testing demonstrated ferritin > 2000 μg/L and/or TSAT ≥ 40%. These markers will be measured prior to administration of Arm A or B treatment. For both Arms A and B, if the serum ferritin level is < 700 μg/L and TSAT < 40%, rescue therapy is administered. All treatment is administered during dialysis via the ports on the dialysis circuits (see additional file 2).

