#### Intervention treatment Arm A and the control Arm B

Intravenous iron polymaltose is administered according to the standard clinical protocol during haemodialysis. For Arm A, patients receive IV iron polymaltose 200 mg during each of the first 2 haemodialysis sessions at the start of the study, and during each of the first 2 dialysis sessions of the week following the monthly blood tests for all subsequent months (i.e. 400 mg per month). If monthly testing demonstrates ferritin > 2000 μg/L and/or TSAT ≥ 40%, IV iron is withheld for the month. The IV iron is restarted as per protocol when the monthly tests demonstrate ferritin > 700 μg/L and ≤ 2000 μg/L and TSAT < 40%. Rescue therapy of 400 mg of iron polymaltose is administered intravenously on haemodialysis if ferritin ≤ 700 μg/L and TSAT < 40% or as indicated by the treating nephrologist (see below). If monthly testing demonstrates ferritin > 700 μg/L and ≤ 2000 and TSAT < 40%, patients will continue with their allocated randomised treatment (Fig. 2).

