### Criteria for discontinuing or modifying allocated interventions {11b}

#### Rescue therapy

For both Arms A and B, if monthly blood tests demonstrate ferritin **<** 700 μg/L and TSAT **<** 40%, 200 mg of intravenous iron polymaltose is administered during each of the first two haemodialysis sessions in the second week after the monthly blood tests. When the monthly blood tests indicate ferritin **>** 700 μg/L and ≤ 2000 μg/L and TSAT **<** 40%, the rescue therapy will be ceased, and participants continue to receive their allocated study treatment.

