#### Withholding of therapy

For both arms, if monthly blood tests demonstrate ferritin ***>*** 2000 μg/L and/or TSAT ≥ 40%, study treatment is withheld. When the monthly blood tests indicate ferritin ≤ 2000 μg per litre and TSAT ***<*** 40%, patients continue to receive their allocated study treatment.

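### The monthly ferritin and TSAT treatment rules contradict each other below 700 μg/L, at exactly 700 μg/L and on restart after withholding, so they need reconciling into one set of ranges by arm

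*Protocol article*

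**What the plan says.** Five places in the protocol article turn the monthly ferritin and TSAT results into treatment.

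- *Treatment of study participants* {11a}: Arm A receives "monthly intravenous iron if serum ferritin ≥ 700 μg/L and ≤ 2000 μg/L and TSAT < 40% (Arm A"; Arm B receives none. Rescue is separate: "For both Arms A and B, if the serum ferritin level is < 700 μg/L and TSAT < 40%, rescue therapy is administered".
- *Intervention treatment Arm A and the control Arm B*: 400 mg of rescue iron is due at ferritin ≤ 700 with TSAT < 40%. Allocated treatment continues, and iron restarts after withholding, only at > 700 and ≤ 2000. Assigned iron is given "during each of the first 2 dialysis sessions of the week following the monthly blood tests for all subsequent months".
- *Rescue therapy* {11b}: in both arms, at ferritin < 700 with TSAT < 40%, 200 mg "is administered during each of the first two haemodialysis sessions in the second week after the monthly blood tests". Once ferritin is > 700 and ≤ 2000 with TSAT < 40%, "the rescue therapy will be ceased, and participants continue to receive their allocated study treatment".
- *Withholding of therapy* {11b}: treatment stops at ferritin > 2000 and/or TSAT ≥ 40%. Once ferritin is ≤ 2000 and TSAT < 40%, "patients continue to receive their allocated study treatment". No lower ferritin limit is given.
- *Safety* {23}: "Assigned study drug will be administered for ferritin levels between" 700 and 2000 with TSAT < 40%, and also below 700 with TSAT < 40%, for Arm A. Arm B has no treatment at 700 to 2000, and both arms have rescue below 700. The next item states that rescue is what both arms receive in that month when ferritin is below 700 and TSAT below 40%.

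**The concern.** The rules are applied to every participant's monthly bloods for up to 36 months, in several units, by staff who know the allocation. Where two sections answer the same result differently, a unit can follow the protocol and still treat differently from its neighbour. Three things depend on the answer:

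- the iron a patient receives, which is a safety matter;
- the iron given in Arm B, and so the contrast that the trial tests and the tertiary outcome of cumulative iron dose;
- the per-protocol population under {20c}, defined as those who completed treatment as allocated. Membership cannot be settled while the text disagrees on what was due. The same holds for the adherence checks on medical records and for the monitor's verification of study drug.

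**Working it through.** **Amounts.** Assigned iron is 2 × 200 = 400 mg per month, which reproduces the protocol's stated monthly amount. Rescue is also 2 × 200 = 400 mg. Both in one month would be 400 + 400 = 800 mg.

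**Each section's rule, with TSAT < 40% throughout** (assigned + rescue, in mg):

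| Section | < 700, Arm A | < 700, Arm B | Exactly 700, Arm A | Exactly 700, Arm B |
|---|---|---|---|---|
| Treatment of study participants | 0 + 400 | 0 + 400 | 400 + 0 | 0 + 0 |
| Intervention treatment Arm A and the control Arm B | 0 + 400 | 0 + 400 | 0 + 400 | 0 + 400 |
| Rescue therapy | 0 + 400 | 0 + 400 | not covered | not covered |
| Safety, literal text | 400 + 400 | 0 + 400 | 400 + 0 | 0 + 0 |

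Just above the threshold (checked at 701) the four sections agree: 400 mg assigned in Arm A and none in Arm B.

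**1. Below 700.** All four sections give rescue in both arms. The conflict is whether Arm A's assigned iron is due as well. Three sections make the two alternatives; the Safety sentence lists the range under both. Literal reading: 800 mg against 400 mg, in Arm A only. The timing does not exclude both courses, because assigned iron falls in the week following the bloods and rescue in the second week.

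**2. Exactly 700.** Two sections place this value with allocated treatment (≥ 700) and one with rescue (≤ 700). The Rescue therapy section neither triggers rescue (< 700) nor returns the patient to allocated treatment (> 700). In Arm A the amount is 400 mg wherever a rule applies; only its label and week change. In Arm B it is 0 or 400 mg.

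**3. Restart after withholding.** Because TSAT ≥ 40% alone triggers withholding, a patient can leave it with ferritin below 700.

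| Section | Ferritin for restart | Arm B patient now < 700, TSAT < 40% |
|---|---|---|
| Intervention treatment Arm A and the control Arm B | > 700 and ≤ 2000 | no restart; rescue, 400 mg |
| Withholding of therapy, read alone | ≤ 2000 | allocated treatment, 0 mg |
| Rescue therapy | < 700 triggers rescue | rescue, 400 mg |

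For an Arm A patient in this position, the Withholding section alone gives 400 mg as assigned iron and the Rescue therapy section 400 mg as rescue.

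**The case against.** A reader might infer that the Safety section authorises two courses in a month. The documents do not support that as the intended rule. The next item in the same section names only rescue for that month. The section describes its purpose as avoiding both too much and too little iron. *Explanation of choice of comparators* {6b} cites 400 mg as the monthly maximum in the standard protocol for ferritin < 700 with TSAT < 40%. Both courses are the same drug in the same amount, so the clause may mean only that Arm A still receives iron there, labelled rescue. Different weeks show that each course has a slot, not that both apply. This objection stands against 800 mg as an intended dose. It does not remove the sentence that lists one range under two treatments.

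The restart conflict is also softer than it looks. The Rescue therapy section covers both arms and any monthly test, with no exception after withholding. Read together, the sections point to rescue, and the conflict arises when the Withholding section is read alone. Even so, the two restart conditions are stated differently.

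The exact-700 conflict concerns a single value, and the protocol gives no frequency for it. Figure 2, additional file 2 and the site procedures are not shown and may make the intent clear. They would not correct the wording here.

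A reader might also count the clause allowing rescue "or as indicated by the treating nephrologist (see below" as a contradiction. It is not one: the abstract likewise allows rescue on clinical grounds, and a fuller definition would be added detail.

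**Conclusion.** The rules are inconsistent as written and should be corrected. The firmest conflict is at ferritin exactly 700, where an Arm B patient is due 0 or 400 mg depending on the section. After withholding, an Arm B patient below 700 is due 0 mg if the Withholding section is read alone and 400 mg under the Rescue therapy section. Below 700 in Arm A, 400 mg is the better-supported reading and 800 mg only a literal one, but the sentence that permits it stands in the section meant to guard against excess.

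These amounts assume TSAT < 40% and full courses given as described. How many patient-months are affected cannot be derived from the protocol, so no effect on the treatment estimate or on power is claimed. The primary analysis is by intention to treat, and its method is unaffected. What is exposed is consistency of treatment between units, the iron contrast through Arm B, and the secondary per-protocol analysis. Which rule is clinically right is not judged here.

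**What to change.** Reconcile the five sections into one table of non-overlapping ferritin and TSAT ranges by arm. Every value, including exactly 700, should fall in one row, and each row should state what is given and in which week. The state after withholding should follow from the same rows. Use the table identically in *Treatment of study participants*, *Intervention treatment Arm A and the control Arm B*, *Rescue therapy*, *Withholding of therapy*, *Safety* and the site procedures. The clinical team decides which rule holds in each row.

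Then tie the per-protocol definition in {20c} to that table, so that a month counts as treated as allocated when it matches its row.

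The cost is wording in the protocol and site procedures, a short notice to units already recruiting, and the notification to the ethics committees that {25} requires for any amendment. No change to sample size, randomisation or the primary analysis is needed.

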### Plans for communicating important protocol amendments to relevant parties (e.g. trial participants, ethical committees) {25}

The investigator will inform the HRECs of the following:
All protocol amendments, informed consent changes or revisions of other documents originally submitted for review.Serious and/or unexpected adverse events attributable to study drugsNew information that may affect the safety of the participants or the proper conduct of the trial.Annual updates of study progressTermination of the study including provision of a final study report.

### Dissemination plans {31a}

#### Communicating trial results

The trial results will be communicated to all investigators and to IRG members prior to publication or presentation. The trial results will be presented at national and international scientific conferences. The trial results will also be submitted for publication to a peer-reviewed scientific journal, irrespective of the results. The FNRG will advise on participant and community feedback content and method of delivery. A plain-language summary of the trial results will be made available to individual participants.

## Discussion

The INFERR clinical trial will address significant uncertainty on the safety and efficacy of iron therapy in First Nations Australians with ESKD with hyperferritinaemia and evidence of iron deficiency. This will hopefully lead to the development of evidence-based guidelines. It will also provide the opportunity to explore the causes of hyperferritinaemia. Anaemia, and particularly, iron deficiency anaemia, is common among First Nations ESKD patients from the NT. The coexistence of hyperferritinaemia, inflammation and chronic infections complicates the diagnosis and management of iron deficiency in First Nations patients with CKD/ESKD which the trial will address [6].

The study will also evaluate the significant issues on the performance differences in ferritin measurement platforms to determine clinical decision limits in people with CKD/ESKD [6]. Identifying and evaluating patients with hepatic diseases such as hepatic steatosis and non-alcoholic fatty liver disease (NAFLD) as seen in high prevalent diabetes mellitus, metabolic syndrome states, dialysis dependence and dysmetabolic iron overload will help to adapt iron dosage and to monitor the safety of IV iron therapy in this setting [54–56].

Indiscriminate IV iron therapy has recently been shown to either trigger or aggravate NAFLD in dialysis patients which warrants the evaluation in the INFERR clinical trial [38, 54].

The use of FerriScans, recently shown to accurately measure hepatic iron load in dialysis patients will provide useful information for decision, choice and follow-up of iron therapy in patients with hyperferritinaemia and evidence or iron deficiency [34, 36].

## Trial status

Protocol version number: INFERR trial protocol 2.0

Began recruitment: 16 December 2020.

Approximate date when recruitment will be completed: 30 June 2023.

## Abbreviations

ACTRN: Australian clinical trials registration number
ANZCTR: Australian New Zealand Clinical Trials Registry
AE: Adverse event
ADR: Adverse drug reaction
CA: Central Australia
CAHREC: Central Australia Human Research Committee
CKD: Chronic kidney disease
CARI: Australian and New Zealanders with Kidney Impairment
CRP: C-reactive protein
CI: Chief investigator
CONSORT: Consolidated Standards of Reporting Trials
CV: Cardiovascular
CWS: Clinical workstation
CRF: Case Report Form
CTN: Clinical Trial Notification
DRIVE: Dialysis Patients’ Response to IV Iron with Elevated Ferritin
DSMB: Data Safety and Monitoring Board
ESKD: End-stage kidney disease
ESA: Erythropoietin-stimulating agents
EPO: Erythropoietin
eCRF: Electronic Case Report Form
EDC: Electronic Data Capture
ERI: Erythropoietin Resistance Index
HbA1c: Glycated haemoglobin
Hb: Haemoglobin
HREC: Human Research Ethics Committees
HF: Heart failure
HRN: Hospital registration number
ICJME: International Committee of Medical Journal Editors
IL-1: Interleukin-1
IL-6: Interleukin-6
ID: Identification
IV: Intravenous
IR: Inter-quartile range
FNRG: First Nations Reference Group
KDIGO: Kidney Disease: Improving Global Outcomes
KDOQI: Kidney Disease Outcomes Quality Initiative
LFTs: Liver function tests
MHD: Maintenance haemodialysis
MCV: Mean corpuscular volume
MRI: Magnetic resonance imaging
MI: Myocardial infarction
MCHC: Mean corpuscular haemoglobin concentration
NHMRC: National Health and Medical Research Council
NICE: National Institute for Health and Care Excellence
NT: Northern Territory
PCIS: Primary Care Information System
PHRC: Percentage of hypochromic red blood cells
PIVOTAL: Proactive IV irOn Therapy in haemodiALysis patients
SOPs: Standard operating procedures
SD: Standard deviation
SAE: Serious adverse events
SUSAR: Suspected unexpected serious adverse reactions
REDCap: Research electronic data capture
RBC: Red blood cells
TGA: Therapeutic Goods Administration
TSAT: Transferrin saturation
TIBC: Total iron-binding capacity
TNF-α: Tumour necrosis alpha
